## Abstract

**Introduction:**

Patients with chronic atrophic gastritis (CAG) and intestinal metaplasia (IM) are at risk of developing gastric adenocarcinoma. Their diagnosis and management currently rely on histopathological guidance after random endoscopic biopsy sampling (Sydney biopsy strategy). This approach has significant flaws such as under-diagnosis, poor reproducibility and poor correlation between endoscopy and histology. This prospective, international multicentre study aims to establish whether endoscopy-led risk stratification accurately and reproducibly predicts CAG and IM extent and disease stage.

**Methods and analysis:**

Patients with CAG and/or IM on standard white light endoscopy (WLE) will be prospectively identified and invited to undergo a second endoscopy performed by an expert endoscopist using enhanced endoscopic imaging techniques with virtual chromoendoscopy. Extent of CAG/IM will be endoscopically staged with enhanced imaging and compared with standard WLE. Histopathological risk stratification through targeted biopsies will be compared with endoscopic disease staging and to random biopsy staging on WLE as a reference. At least 234 patients are required to show a 10 % difference in sensitivity and accuracy between enhanced imaging endoscopy-led staging and the current biopsy-led staging protocol of gastric atrophy with a power (beta) of 80 % and a 0.05 probability of a type I error (alpha).

**Ethics and dissemination:**

The study was approved by the respective Institutional Review Boards (Netherlands: MEC-2018-078; UK: 19/LO/0089). The findings will be published in peer-reviewed journals and presented at scientific meetings.

**Trial registration number:**

NTR7661; Pre-results.

Strengths and limitations of this studyThis is the first study to compare endoscopy-led risk stratification of premalignant gastric lesions using advanced imaging and targeted biopsies with white light endoscopy and random biopsies as a reference, performed at separate occasions with the endoscopist blinded to prior results.This study will additionally provide biobank biopsy and serum material for future biomarker analysis.A possible limitation of this study is that all procedures will be performed by expert endoscopists in teaching hospitals, therefore external reproducibility will be evaluated using interobserver variability of disease staging through video recordings.The same limitation holds for the histopathological evaluation of the biopsy samples for which a proportion of the samples will be reviewed and rescored by a blinded second expert gastrointestinal histopathologist.

## Introduction

Gastric adenocarcinoma remains a major cause of cancer mortality and is the most commonly diagnosed malignant condition of the gastrointestinal (GI) tract.^1–4^ Although incidence rates had previously been declining, recent studies demonstrated this differs among population subgroups. For example, an increasing incidence of gastric adenocarcinoma among young white cohorts in Western countries was objectified. This may be due to an increasing prevalence of gastric cancer precursors among younger adults, in particular chronic atrophic gastritis (CAG), intestinal metaplasia (IM) and dysplasia.^5 6^ These studies suggest that gastric cancer incidence rates may plateau or even increase again in the upcoming years. Importantly, with the exception of Japan and Korea, the majority of gastric cancers worldwide are diagnosed at later stage. This results in a poor prognosis with less than 30% 5 year survival.^1 2 7^ Japan’s earlier stage of diagnosis and superior 5 year survival highlight the need for earlier recognition and treatment.^8^

Endoscopic recognition of the premalignant stomach has long been problematic and limited by the ability of endoscopist and the imaging tools. A previous study demonstrated that 22% of high-grade dysplastic lesions and early gastric cancers were missed.^9 10^ A meta-analysis and systematic review of endoscopy follow-up studies confirmed that a marked proportion of early gastric cancers are missed at endoscopy.^10^ Therefore, current practice uses histology-based staging.^11 12^ However, endoscopic imaging has significantly improved with high-definition endoscopes and imaging enhancement technologies now routinely available. Some recent studies already suggested that accurate endoscopic staging of CAG and gastric intestinal metaplasia (GIM) is achievable and can robustly predict gastric adenocarcinoma risk. Importantly, the interobserver and intraobserver reproducibility characteristics of endoscopic CAG and GIM severity assessment are in experienced hands moderate to excellent.^13–18^ These marked improvements in endoscopic technology and the shift towards an endoscopy-led approach will empower the endoscopist to risk stratify individuals with greater accuracy and decrease the already huge burden placed on our endoscopy and histopathology departments. Therefore, the aim of this study is to evaluate if enhanced endoscopic imaging, including high-definition white light endoscopy (WLE) and virtual chromoendoscopy, alongside targeted biopsies, provides an accurate and reproducible assessment of CAG and IM disease extent and staging, when compared with the current practice of WLE and random biopsies through the Sydney protocol biopsy strategy.

## Methods and analysis

### Aims

The primary aim of this study is to assess the diagnostic accuracy for the endoscopic diagnosis of IM in Sydney biopsy locations comparing standard endoscopic staging with random biopsies with enhanced imaging with biopsies targeted to GIM.^19^ The Standards for Reporting of Diagnostic Accuracy Studies (STARD) guidelines were followed.^20^ Study sites are located in the Netherlands and the UK. Secondary objectives are to evaluate (a) reproducibility of endoscopic staging after expert review, (b) reproducibility of histopathology for detection of IM, (c) the number of dysplastic or neoplastic lesions detected and (d) effects of inspection time of gastric mucosa on diagnostic accuracy.

### Design

This is a prospective, multicentre registry study on the accuracy and reproducibility of enhanced endoscopic imaging, including high-definition WLE and virtual chromoendoscopy, for the staging of CAG and IM. Two upper endoscopies will be performed on two separate occasions (6–12 months in between) using standard white-light endoscopy plus random biopsies (current diagnostic strategy) at the first endoscopy and enhanced endoscopic imaging with targeted biopsies (proposed diagnostic strategy) at the second endoscopy. We will compare both approaches using histopathology as a reference and assess the accuracy and reproducibility of enhanced endoscopic imaging (figure 1).

**Figure 1 F1:**
[figure not shown]
Flowchart of the study design. CAG, chronic atrophic gastritis; EGGIM, endoscopic grading of gastric intestinal metaplasia; GI, gastrointestinal; *H. pylori,*
*Helicobacter pylori*; OLGA, operative link for gastritis assessment; OLGIM, operative link for gastric intestinal metaplasia assessment; WLE, white light endoscopy.

## Patient and public involvement

We maintained close links with patient alliances and interest groups, both in the Netherlands as well as in the UK. This close relationship informs our practice and is the basis for the current study design. We will engage closely with patient interest groups to communicate research findings and ensure that our deliverables are fit for purpose.

## Participants

### Sample size

For estimation of sample size, we assume that the diagnosis of CAG or IM on enhanced imaging and targeted biopsies must be set with at least a 90% sensitivity with WLE and random biopsies as a reference.^15^ A power (beta) of 80% and a probability of type I error (alpha) of 0.05 will be handled. That purpose requires at least 234 patients to be recruited to show a 10 % difference in sensitivity between enhanced endoscopy-led staging and the standard WLE.

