### Recruitment

All patients (>18 years of age) referred to the endoscopy department for routine diagnostic upper GI endoscopy and diagnosed with CAG or IM between November 2018 and June 2020 are eligible for inclusion if able to give informed consent. Patients are excluded when having (1) gastric neoplasia not amenable to endoscopic resection, (2) no indication for Sydney biopsy staging on standard WLE, (3) significant comorbidity, (4) a coagulation disorder, (5) previous gastric surgery or (6) are unable to complete the biopsy protocol in either endoscopy session.

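### The sample-size objective scores white light endoscopy with random biopsies against itself, so the powered 10-point sensitivity gain cannot arise as worded

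*Protocol article*

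**What the plan says.** The Sample size section of the protocol article sets a condition for the enhanced strategy: a CAG or IM diagnosis reached by that route "must be set with at least a 90% sensitivity with WLE and random biopsies as a reference". It then asks for at least 234 patients, at 80% power and alpha 0.05, to show a 10-point "difference in sensitivity between enhanced endoscopy-led staging and the standard WLE".

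The abstract (Methods and analysis) words the comparator as the whole standard strategy: the difference is "between enhanced imaging endoscopy-led staging and the current biopsy-led staging protocol of gastric atrophy". The same paragraph takes "random biopsy staging on WLE as a reference". The strengths and limitations box has similar wording, "with white light endoscopy and random biopsies as a reference".

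The Design section gives another rule: "We will compare both approaches using histopathology as a reference". The Statistical analyses section agrees with Design. It defines accuracy per biopsy, by whether the histology of the directed biopsies confirms the endoscopic impression.

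Three other statements matter:
- **Entry:** patients "diagnosed with CAG or IM between November 2018 and June 2020 are eligible for inclusion" (Recruitment). The abstract and the White light endoscopy section place that finding at the standard endoscopy.
- **Primary aim:** diagnostic accuracy for IM by Sydney biopsy location (Aims).
- **Second endoscopy:** areas judged free of IM are also biopsied, as controls, so every Sydney area has second-session histology (Enhanced imaging endoscopy).

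**The concern.** A sensitivity comparison needs a reference on which either strategy can fail. In the Sample size section, read with the abstract, one strategy is both the reference and the comparator. It cannot miss anything that it defines. Enhanced imaging can tie with it or lose to it.

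This conflicts with the article's premise, stated in the abstract, that random sampling under-diagnoses. IM that enhanced imaging finds where the earlier random biopsy missed it would count as a false positive.

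The two reference rules also lead to different conclusions from the same data. If the analysis follows Sample size, the powered objective can only show a deficit. If it follows Design and Statistical analyses, the 234 is no longer tied to the comparison being made.

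**Working it through.** **1. Reproducing 234.** From the article: enhanced sensitivity 90%, difference d = 0.10, power 80%, alpha 0.05, two-sided tests, each patient examined both ways. Not in the article, and assumed here: WLE sensitivity 80%, and the discordant share ψ = p10 + p01. Here p10 is the share of reference-positive patients found by enhanced imaging only, and p01 the share found by the standard strategy only.

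McNemar size: n = [1.96·√ψ + 0.8416·√(ψ − d²)]² / d²

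| Case | p10 | p01 | ψ | n |
|---|---|---|---|---|
| Maximum discordance | 0.20 | 0.10 | 0.30 | 233.1, so **234** |
| Independent errors | 0.18 | 0.08 | 0.26 | 201.7, so 202 |
| Minimum discordance | 0.10 | 0 | 0.10 | 76.1, so 77 |

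First row: (1.96 × 0.5477 + 0.8416 × 0.5385)² / 0.01 = (1.0735 + 0.4532)² / 0.01 = 233.1.

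Unpaired 90% versus 80% gives 199 per arm (219 with continuity correction). A one-sample test of 80% versus 90% gives 108 (118 with correction). Neither matches. The match with 234 is exact, but it rests on two inputs that the article does not state, so it suggests the origin without proving it.

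**2. The same quantities under the Sample size reference.** The reference is WLE plus random biopsies.
- Sensitivity of the standard strategy: 234/234 = 100%.
- Enhanced imaging at its 90% target: 0.90 × 234 = 210.6, about 211/234.
- p10 = 0, because no reference-positive patient can be missed by the strategy that defines positivity. p01 = 0.10.
- Difference: 90% − 100% = −10 points. The upper limit of the difference is 0 at any sample size.

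Showing a deficit of this size needs (1.96 × √0.10 + 0.8416 × √0.09)² / 0.01 = 76.1, so 77 reference-positive patients. With 234 the power to show it is about 99.9%. The calculation that yields 234 needs p10 = 0.20, whereas the stated reference forces p10 = 0.

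**3. The entry rule.** For the patient-level diagnosis of CAG or IM, every entrant is positive at the first endoscopy. Among entrants who are positive on any reference, the standard strategy has missed none, so p10 = 0 again.

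**4. The location-level comparison.** Entry needs CAG or IM somewhere in the stomach. A single Sydney location can be IM-negative at the first session, and a patient with CAG only can enter with no IM. With second-session or combined histology as reference, p10 can exceed 0. If 234 reference-positive units were independent and the sensitivities were 80% and 90%, power would be 80.2% at maximum discordance and 85.6% with independent errors. Locations within a patient are not independent, so these powers do not carry over directly.

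**5. Illustration of gains scored as errors.** Assume IM in 40% of locations, enhanced imaging 90% sensitive and 90% specific, and a share r of IM-positive locations detected by random biopsy. Against the random-biopsy reference:

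Apparent specificity = 1 − [0.4(1 − r)·0.9 + 0.6·0.1] / (1 − 0.4r)

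- One biopsy per location, r = 0.5 to 0.8: 70% to 81%, instead of 90%.
- Two to four biopsies per area, as the Sydney scheme in the article takes, each detecting 50% independently: r = 1 − 0.5² = 0.75 to 1 − 0.5⁴ = 0.94, giving 79% to 87%.

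None of these inputs is in the article, and a lower IM prevalence shrinks the effect. The illustration shows direction only.

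**The case against.** **The operative sections already use histopathology.** Aims, Design, Enhanced imaging endoscopy and Statistical analyses together describe a location-level comparison in which IM found only by enhanced imaging and confirmed on biopsy is a true positive. This stands, and it limits the point to the powered objective and to the patient-level diagnosis. It does not remove the contradiction, because the sample size is attached to the other rule.

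**The word reference may mean comparison strategy.** In the abstract and the strengths box that is a fair reading. In Sample size it is not, because the clause qualifies a sensitivity figure and so names the truth standard.

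**Standard WLE may mean the visual impression alone.** Its sensitivity against random biopsies would then not be 100% by definition. The Sample size section taken alone allows this, but the abstract's comparator, the biopsy-led protocol, does not.

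**The 77-versus-234 contrast proves little.** Agreed. It fits a loosely worded sentence as well as a broken calculation. The flaw lies in the wording, and the arithmetic only shows what that wording implies.

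**A stronger inference.** A reader might conclude that this study can never show enhanced imaging to be better, and that it has no reference-negative patients. The documents do not support either. Both statements hold only under the Sample size reference or for the patient-level composite of CAG or IM. Patients with CAG only can be IM-negative, and individual locations can be negative in any patient.

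**Conclusion.** The point holds in limited form and needs correction before analysis. The article states two incompatible reference standards: Sample size, with the abstract and similar wording in the strengths box, against Design and Statistical analyses. Under the first, the standard strategy is 100% sensitive by construction, the largest possible gain is 0 points against the 10 powered, and any difference is a deficit of enhanced imaging. For the patient-level diagnosis of CAG or IM, the entry rule has the same effect under any reference.

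The location-level IM comparison escapes this and can show a gain. The 0-point limit follows from the wording and needs no outside figure. The account of how 234 arose depends on an assumed WLE sensitivity of 80% and discordance of 30%.

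**What to change.** 1. In Sample size, delete the closing clause that makes WLE with random biopsies the reference, and align the abstract and the strengths box with the Design section.
2. State one histological reference per Sydney location. For example, a location is IM-positive if histology from it is positive at either session, with second-session histology alone as a sensitivity analysis.
3. Score both strategies by location within patient. A positive control biopsy in an area judged free of IM at the second endoscopy counts as a miss for enhanced imaging. Test the paired difference in sensitivity with allowance for clustering.
4. Do not report patient-level sensitivity for CAG or IM.
5. Restate the basis of 234: the assumed WLE sensitivity, the discordance, the unit of analysis and the clustering.

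The alternative is to keep WLE biopsies as the yardstick and recast the target as at least 90% positive agreement with them, with no superiority claim.

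**Cost.** The biopsies needed are already planned at both sessions. The work is rewording plus a new sample-size calculation, which may not return 234.

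**Limits to state with the fix.**
- The composite contains each strategy's own biopsies, so specificity should be reported for the endoscopic impression and not for the biopsy result. Second-session histology alone rests on the enhanced strategy's own biopsies and does not remove this problem.
- With 6–12 months between sessions, real change cannot be separated from a miss.
- Selection on first-session positivity favours WLE. Targeted biopsies in the reference and protocol experts at the second session favour enhanced imaging. The net direction is unknown, so a gain should not be called conservative.

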### Statistical analyses

For descriptive statistics, mean (±SD) will be used in case of a normal distribution of variables and median (25–75%) will be used for variables with a skewed distribution. Where appropriate, the Student’s t-test or Mann–Whitney U test will be used.

Diagnostic accuracy of endoscopic diagnosis of CAG and IM is defined as the total number of directed biopsies that confirm the endoscopic impression of the presence or absence of IM divided by the total number of biopsies (accuracy=true positives+true negatives/all biopsies). Results will be compared with the histopathology outcomes using the χ^2^ test after multiple testing correction as well as kappa values for interobserver agreement among endoscopists and histopathologists.

After study completion, all videos will be collated and anonymised prior to expert panel review and estimation of the severity and extent of atrophy as well as IM. Five expert reviewers will review 50 videos each (kappa 0.4) for the purposes of assessing interobserver reliability. Sensitivity, specificity and global accuracy along with the 95% confidence intervals will be established. Duration of inspection time of gastric mucosa and its relation to diagnostic accuracy will be evaluated using, when appropriate, a paired t-test or Wilcoxon test. All tests will be two-sided.

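### The 80% power for 234 patients is claimed at an uncorrected alpha of 0.05, but accuracy is to be tested after multiplicity correction, so that power is not supported for the accuracy test

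*Protocol article*

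**What the plan says.** In the protocol article, the Sample size section gives the error rates: "A power (beta) of 80% and a probability of type I error (alpha) of 0.05 will be handled". It ties them to one measure: "at least 234 patients to be recruited to show a 10 % difference in sensitivity between enhanced endoscopy-led staging and the standard WLE". The assumed level for enhanced imaging is that the diagnosis "must be set with at least a 90% sensitivity with WLE and random biopsies as a reference". No comparator sensitivity, within-patient discordance or dropout rate is given.

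The Methods and analysis paragraph of the abstract repeats the number, the power and the alpha, but for two measures: "At least 234 patients are required to show a 10 % difference in sensitivity and accuracy between enhanced imaging endoscopy-led staging".

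The Aims section makes diagnostic accuracy for intestinal metaplasia by Sydney location the primary aim. The Statistical analyses section defines that accuracy per biopsy ("accuracy=true positives+true negatives/all biopsies") and continues: "Results will be compared with the histopathology outcomes using the χ^2^ test after multiple testing correction". It also states "All tests will be two-sided". It does not name the correction method or the family of tests, and it sets no comparison apart as exempt.

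**The concern.** Power is a property of a test at a given significance level. The abstract claims 80% power at 0.05 for accuracy, and the analysis section tests accuracy at a level stricter than 0.05 by an unstated amount. Both statements are in the printed text, and they do not fit together.

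Two things are at stake. The study may have less chance than stated of confirming the difference for which it was sized. And if the accuracy p-value falls between the corrected level and 0.05, the article does not settle whether the primary aim was met. Both problems are avoidable, because a single primary comparison declared in advance needs no correction for secondary ones.

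**Working it through.** **Inputs stated.** 234 patients, 80% power, alpha 0.05, a 10% difference and 90% sensitivity for enhanced imaging (Sample size); two-sided tests (Statistical analyses); both endoscopies in the same patients (Design); 10 Sydney biopsies at the first endoscopy (White light endoscopy).

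**Inputs assumed.** Comparator sensitivity 80% (the 10% read as absolute), Bonferroni correction, and *m* = 2 to 10 corrected tests. The article states none of these.

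**Step 1: the plan's own figure.** 234 does not follow from the stated inputs alone. Two independent proportions, 0.90 versus 0.80, need 199 per group (219 with continuity correction). For a paired comparison with total discordance ψ and difference *d* = 0.10,

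n = (z₁₋α/₂·√ψ + z₁₋β·√(ψ − d²))² / d².

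- At ψ = 0.26 (misses independent: 0.10 + 0.20 − 2 × 0.02), n = 201.7, so 202.
- At ψ = 0.30 (no patient missed by both strategies, the maximum for these rates), n = (1.960 × 0.5477 + 0.8416 × 0.5385)² / 0.01 = 233.1, so 234.

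The second line matches, but only with a discordance the article does not give. Another unstated input comes almost as close: 199 / (1 − 0.15) = 234.1, or 235 after rounding up, with 15% dropout. None of these routes includes an allowance for multiplicity.

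**Step 2: effect of the correction if 234 gives exactly 80% at two-sided 0.05.** This needs no view on how 234 was obtained. Power = Φ(1.960 + 0.842 − z), where z is the critical value at 0.05/*m*.

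| *m* | critical z | power | patients to restore 80% |
|---|---|---|---|
| 2 | 2.241 | 71% | 284 |
| 3 | 2.394 | 66% | 313 |
| 5 | 2.576 | 59% | 349 |

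The last column is 234 × ((z + 0.842) / 2.802)², rounded up.

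**Step 3: dependence on discordance.** Paired test, 90% versus 80%, n = 234; power = Φ((d√n − z√ψ) / √(ψ − d²)).

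| ψ | *m* = 1 | 2 | 3 | 5 |
|---|---|---|---|---|
| 0.30 | 80.2% | 71.3% | 65.8% | 58.7% |
| 0.26 | 85.6% | 78.0% | 73.2% | 66.7% |
| 0.20 | 93.3% | 88.7% | 85.4% | 80.7% |

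For two tests, power reaches 80% once ψ is about 0.249 or less. That is 2.55% of patients missed by both strategies, a within-patient correlation of (0.0255 − 0.02) / √(0.09 × 0.16) = 0.05.

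**Step 4: dependence on the unit.** The accuracy definition counts biopsies: 234 × 10 = 2340 per endoscopy, assuming ten at the second as well. With design effect 1 + 9 × ICC (ICC assumed) and 0.90 versus 0.80 treated as two samples:

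| ICC | effective n | *m* = 2 | 5 | 10 |
|---|---|---|---|---|
| 0.3 | 632 | 99.7% | 99.2% | 98.6% |
| 0.5 | 425 | 97% | 94% | 90% |
| 0.8 | 285 | 87% | 78% | 71% |

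A biopsy-level test would therefore fall below 80% only with very strong clustering and several corrected tests.

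**The case against.** The strongest reply is that the corrected test is not shown to be the sized test. The Sample size section powers a patient-level contrast in sensitivity between strategies. The correction sentence follows a biopsy-level definition of accuracy and speaks of comparison with histopathology. This stands as far as sensitivity goes: the article does not show that the sensitivity contrast is corrected. It does not rescue accuracy, for which the abstract claims the same power at the same alpha.

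Second, a reader might infer that power actually falls below 80%, to 71% or less. The documents do not support that. The 71% depends on two tests, on Bonferroni, and on 234 giving no more than 80% at 0.05. Two examinations of the same stomach would ordinarily agree more than chance, and a very small positive correlation is enough to keep 80% for two tests. A fixed-sequence or gatekeeping procedure would leave the first test at 0.05. The abstract's two measures need not be the corrected family either, which could be Sydney locations or secondary comparisons. All of this stands, and it limits what can be said about size.

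Third, it is tempting to treat 234 as a worst-case McNemar calculation because the arithmetic matches. Several routes come near 234 and each needs an unstated input, so there is no verified 80% baseline from which to measure a loss.

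Fourth, the method and family of a correction are commonly left to an analysis plan. That is fair, and their absence is not the point here. The point is that two stated rules, an uncorrected alpha behind the power claim and a corrected test of accuracy, are not aligned.

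**Conclusion.** The point holds in limited form. The published 80% power rests on an uncorrected 0.05, the abstract extends it to accuracy, and accuracy is tested after correction with no primary comparison exempted. The 80% is therefore not supported for the corrected accuracy test.

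How much power is lost is open. Step 2 gives an illustrative 71% to 59% for two to five Bonferroni tests; steps 3 and 4 show plausible conditions in which power remains at 80% or above. A stricter alpha always lowers the power of a given test, but whether it falls below 80% depends on discordance, unit of analysis, correction method and number of tests, none of which the article settles well enough. A claim that the study is underpowered would go beyond the text.

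**What to change.** In Statistical analyses, name one primary comparison, enhanced versus standard strategy on a single measure, and test it at two-sided 0.05 without correction. Apply the correction (Holm, for example) only to the remaining comparisons. In the abstract, claim the 80% power for that one measure, so that it agrees with the Sample size section.

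If the correction is meant to cover the primary test, restate the power at the corrected alpha, giving the number of tests, the comparator rate, the unit of analysis and the discordance or clustering assumed.

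The cost is one or two sentences, with no extra patients or procedures. The downside is that the other measure becomes secondary or, under the alternative, that the stated power may be less favourable.
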